# Study protocol for Healthy Conversations @ Playgroup: a multi-site cluster randomized controlled trial of an intervention to promote healthy lifestyle behaviours in young children attending community playgroups

**DOI:** 10.1186/s12889-021-11789-3

**Published:** 2021-09-26

**Keywords:** Obesity, Childhood, Diet, Physical activity, Screen time, Sleep

## Abstract

**Background:**

Early childhood is a critical window for preventing obesity and chronic disease. Yet, 1 in 4 Australian children aged 5 years and under are affected by overweight or obesity; and significant proportions of children under 5 years fail to meet guidelines for diet quality, physical activity (PA), screen time, and sleep. Consequently, effective interventions to promote healthy lifestyle behaviors and prevent obesity during early childhood are needed. Community playgroups provide an opportunity for parents, carers, and children to meet in a safe and relaxed environment to play and share information. The structure, low cost and reach of playgroups provide a unique platform to engage parents in a scalable program to promote healthful lifestyle behaviors and prevent childhood obesity. However, the evidence base for the effectiveness of health promotion programs delivered in community playgroup settings is limited and lacking credible evidence from rigorously conducted randomized controlled trials.

**Methods:**

The Healthy Conversations @ Playgroup randomized controlled trial (RCT) aims to address the underlying behavioral risk factors for obesity by helping parents take effective steps to improve their child’s dietary, PA, screen time, and sleep behaviors. The intervention program comprises 10 “healthy conversations” led by a trained peer facilitator, designed to increase parents’ behavioral capability and self-efficacy to implement autonomy-supportive parenting practices. The program will be delivered biweekly during regularly scheduled playgroup sessions over 10-weeks. Effectiveness will be tested in a 2-arm cluster RCT involving 60 community playgroups in three states across Australia. After baseline assessments, participating playgroups will be randomly allocated to either intervention or wait-list control conditions. Primary outcomes (vegetable intake, discretionary foods, daily PA, screen time, sleep duration, and body mass index [BMI] z-score) will be assessed at baseline, immediately post-intervention (10-weeks; T2) and 6-months post-intervention (T3). Outcomes will be assessed for differential change at T2 and T3.

**Discussion:**

The Healthy Conversations @ Playgroup trial will rigorously evaluate a novel peer-led intervention program to promote healthful lifestyle behaviors and prevent obesity in children and families attending community playgroups. If effective, the program could be immediately scaled-up and delivered in community playgroups across Australia.

**Trial registration:**

Trial registered 22nd January 2021 with the Australian and New Zealand Clinical Trials Registry (ACTRN12621000055808).

**Supplementary Information:**

The online version contains supplementary material available at 10.1186/s12889-021-11789-3.

## Background

Childhood obesity continues to be one of the most serious health challenges worldwide. Globally, it is estimated that over 42 million children aged 0 to 5 years are affected by overweight or obesity [1]. In 2017–18, one in four Australian children aged 5 years or under were affected by overweight or obesity [2]. Of concern, young children with overweight or obesity are more likely to experience significant short-term health problems, including asthma, sleep apnoea, high blood pressure, musculoskeletal disorders, fatty liver disease, and insulin resistance [1, 3]. Compared to peers with a healthy weight, children with overweight or obesity more frequently experience bullying or teasing at school, and are at higher risks of significant mental health issues, including depression, anxiety, and disordered eating, exacerbated by weight stigma and bias [4]. In later life, they are at greater risk of adult obesity, type 2 diabetes, heart disease, certain cancers, obstructive respiratory disease, reproductive disorders, and mental health problems [1, 3]. Consequently, there is an urgent need for effective, scalable, and cost-effective public health interventions to promote healthful lifestyle behaviors and prevent chronic health conditions such as obesity during early childhood.

Healthy eating, regular physical activity, limited screen time, and adequate sleep during the early years are essential for optimal growth and development, cognitive functioning, and prevention of chronic health conditions [5]. Despite this, population-level surveys indicate that significant percentages of young children do not meet public health recommendations for diet quality, physical activity, screen time, and sleep. In Australia, almost half of 2- to 3-year-olds consume less than two servings of vegetables [6]; and discretionary foods such as sweet biscuits, cakes, and processed meats account for one-third of 2- to 3-year-old’s total daily energy intake [7]. Only 35% of 2- to 5-year-olds accumulate at least 180 min of daily physical activity, [8] while 74% of 2- to 4-year-olds exceed the screen time recommendation of less than 1 h per day [9]. Up to 40% of Australian parents report that their infants and young children experience sleep problems and between 10 and 20% of preschool children do not meet current sleep guidelines of 11 to 14 h per 24-h period [10]. Similar trends have been reported in other countries [11].

Intervention studies conducted in home, childcare, and health service settings have demonstrated that obesity-related behaviors can be improved via the promotion of autonomy-supporting parenting practices, and that the rate of change in body mass index (BMI) can be slowed [12]. However, the evidence base is incomplete and substantial gaps in knowledge remain. First, intervention studies conducted to date have primarily targeted obesity-risk behaviors in infants or pre-schoolers, but not toddlers. In a systematic review of obesity prevention trials in children 0 to 5 years, only six of the 23 intervention studies included toddlers (18–36 months) of which one was judged to be of high quality, and none reported significant reductions in BMI [13]. Second, interventions to prevent obesity during early childhood have largely ignored the contribution of sleep to maintaining a healthy weight, despite consistent evidence linking short sleep duration to excess adiposity in children [14, 15]. Third, very few obesity prevention programs have been delivered in existing community-based parent groups where parents have already formed social networks and can learn from and support each other [12].

One such setting, are community playgroups. Community playgroups provide an opportunity for parents, carers, and children to meet in a safe and relaxed environment to play and share information [16]. Open to all families with children under school age, community playgroups present a low-cost, light-touch family support platform because they are run by volunteer parents within a local area, at minimal charge to attending families. Typically, playgroups meet for 2 h per week in a local community venue, sharing unstructured indoor and outdoor play and art/craft activities. Within the early childhood service system in Australia, playgroups form an important, largely universal, bridge between the maternal child health care system and formal early childhood education and care services. They are distinct from other early childhood services because a parent or carer attends with the child and remains responsible for the child during the session. Thus, community playgroups represent an ideal setting to engage parents and deliver programs and services to enhance family functioning and promote child health and wellbeing. They also offer considerable feasibility and efficiency in terms of delivering evidence-based early childhood obesity prevention programs. Community playgroups exist in over 80% of all Australian postcodes in metropolitan, regional, rural, and remote areas [16, 17]. Recent national data indicates that over 50% of children aged 2–3 years attend a playgroup [18].

The structure, low cost and reach of playgroups provide a unique platform to engage parents in a scalable program to promote healthful lifestyle behaviors and prevent childhood obesity. However, the existing evidence base for the effectiveness of health promotion programs delivered in community playgroup settings is limited and lacking credible evidence from rigorously conducted randomized controlled trials. In a systematic review of health promotion programs delivered in playgroups [19], only five publications included nutrition, physical activity, or screen time outcomes, and none focused on sleep. All studies were of low methodological quality, relying on single group pre-post designs and/or qualitative analysis of interviews with playgroup facilitators. Consequently, there is very limited scientific evidence to inform policy makers, service planners, and playgroup facilitators about what works and what does not work when it comes to promoting healthy lifestyle behaviors in playgroup settings.

To bridge this knowledge gap, the Healthy Conversations @ Playgroup study will implement and rigorously evaluate a novel peer-led intervention to promote healthful lifestyle behaviors and prevent obesity in children and families attending community playgroups. The primary aims are: 1) evaluate the effectiveness of a 10-week healthy conversations intervention to improve dietary, physical activity, screen time, and sleep behaviours in children aged 0–5 years; and, 2) examine the impact of the intervention on child BMI z-score at 6-months post-intervention. As secondary aims, the effects of the intervention on parenting practices related to child obesity related behaviors will be examined. It is hypothesised that children in intervention playgroups will exhibit significantly better post intervention diet quality, physical activity, screen time, and sleep behaviors than children attending wait-listed control playgroups. We further hypothesize that children in playgroups allocated to the intervention will exhibit significantly lower BMI z-scores at 6-months post intervention than children attending wait-listed control playgroups.

## Methods

### Study design

To address the study aims, we will conduct a multi-site cluster randomized controlled trial involving 60 community playgroups operating in three states across Australia – Queensland (*n* = 20), South Australia (*n* = 20), and Western Australia (*n* = 20). After baseline assessments, participating playgroups will be randomly allocated to either the intervention or wait-list control conditions. Primary study outcomes will be assessed for differential change immediately post intervention (10-weeks; T2) and 6-months post intervention (T3). An overview of the study design, the schedule for enrolment and study assessments is shown in Table 1.

**Table 1 Tab1:**
[figure not shown]
Schedule of enrolment, intervention, and assessments

Primary outcomes: daily servings of vegetables, daily servings of discretionary foods, percentage of time in moderate-to-vigorous p20hysical activity (MVPA), daily screen time, and sleep duration per 24 h period

Secondary outcomes: parental self-efficacy, parenting practices related to healthy eating, physical activity, screen time, and sleep

^1^ Provided only to parents allocated to the intervention group

### Eligibility criteria

Playgroups meeting the following inclusion criteria will be eligible to participate in the program: located within a 150 km radius of the Queensland Centre for Children’s Health Research, Flinders University, South Australia or Telethon Kids Institute, University of Western Australia; operating as a community playgroup (that is, coordinated by parent volunteers rather than a paid facilitator); and at least four parent-child dyads willing to participate in the evaluation of the program. In each participating playgroup, all parents with children between the ages of 1 and 5 years will be invited to participate in the evaluation. Parents with multiple children within the specified age range will be asked to enroll their oldest child in the study. Parents will be excluded if they are unable to give informed consent or have insufficient literacy to complete data collection. Parents with children outside the target age range or children with chronic health conditions that may adversely influence weight status, physical activity, diet, or sleep (e.g., severe respiratory disease, congenital heart disease), will be able to participate in the program, but will be excluded from the evaluation.

### Recruitment

All eligible community playgroups will receive information about the Healthy Conversations @ Playgroup program through their respective state-level playgroup association via social media, newsletters, email or flyers. Playgroups registering an interest in the program will be contacted by a member of the research team to further explain the project and obtain permission to visit the playgroup. If permission is granted, a research team member will attend a regular playgroup session and explain the project to all parents in attendance. Playgroups will then be given time to discuss and decide if they, as a group, would like to receive the program. If the playgroup elects to receive the program, project staff will initiate the necessary informed consent procedures. Prior to participation, full written and informed consent will be obtained from legal parents/guardians. Parents/guardians will have the option to sign a hard copy of the consent form at the session or use a QR code to access the consent form on-line and sign it electronically. This process will continue until the required number of playgroups with sufficient participants in each site are recruited.

### Sample size and power

For Aim 1, the intervention effect is the net difference for change in the healthy lifestyle behaviors immediately post intervention and at 6-months follow-up. The research hypothesis is that the intervention will result in net differences of 0.5 serving of vegetables (38 g per day), 1.5 servings of discretionary foods per day, 15 min or 2% of time in MVPA, 30 min screen time per day, and 40 min of sleep per 24 h period. The null hypothesis is a net difference of zero. For Aim 2, the intervention effect is the net difference for change in BMI z-score at 6-months follow-up. The research hypothesis is that the intervention will result in a difference of 0.30 BMI z-score units. The null hypothesis is a net difference of zero. For a 2-year-old at the 84th percentile or a BMI z-score of 1.0, a difference of 0.30 z-score units equates to a clinically meaningful reduction of 0.4 kg in excess weight.

Table 2 reports minimal detectable differences for samples of 20, 30, and 40 community playgroups per condition. All calculations were performed assuming a power of 0.80, a 2-tailed alpha level of 0.05, an average cluster size of six parent-child dyads, and an intra-cluster correlation (ICC) of 0.10 and 0.02 for the child health behaviors and BMI z-score, respectively. Standard deviation estimates for vegetable intake were based on dietary intake data from the NOURISH randomized controlled trial [20]. The standard deviations for time in physical activity and screen time were based on previously published studies in Australian children aged 0–5 years [21]. The standard deviation for sleep duration was based on published data on Australian children [10]. The standard deviation for change in BMI z-score was based on data from the NOURISH randomized controlled trial [20]. Based on these calculations, a sample of 30 playgroups per condition achieves ≥80% power to detect the hypothesized between-group differences for each of the primary outcomes. To offset a projected attrition rate of up to 25%, an additional two children within each playgroup will be recruited, providing an overall sample of 60 community playgroups and 480 parent-child dyads.

**Table 2 Tab2:** Minimal detectable differences for child health behaviors and BMI z-score

Study Outcome	Hypothesised Effect	Est. SD	20 Playgroups (***n*** = 120)	30 Playgroups (***n*** = 180)	40 Playgroups (***n*** = 240)
Veg Intake	½ serve, 38 g/d	58 g/d	26 g/d	21 g/d	18 g/d
Discretionary Foods	1.5 serv/d	2 serv/d	1 serv/d	0.7 serv/d	0.6 serv/d
% Time in PA	2.0%	5%	2.2%	1.8%	1.6%
Screen Time	30 min/d	75 min/d	33 min/d	27 min/d	24 min/d
Sleep Duration	40 min/d	96 min/d	43 min/d	35 min/d	30 min/d
BMI z-score	0.30	0.90	0.34	0.28	0.24

### Randomization, allocation, and blinding

Group assignment for each site will be completed by an independent statistician using an allocation sequence generated by permuted block randomization. After baseline assessments, playgroups in each site will be randomized to the next condition (intervention or wait-list control) on the list using the database randomization module in the Research Electronic Data Capture (REDCap) platform hosted at The Queensland University of Technology [22]. Trained assessors blinded to group allocation will collect the primary and secondary outcome data. Within a health behavior intervention, it is not possible to blind either the persons delivering the intervention (peer facilitators – see below) or participants; however, peer facilitators will not take part in outcome assessments.

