### Signposting intervention

Between each session, parents will receive ‘signposts’ directing them to information and support about the topics covered. These signposts will be delivered via social media, using private Facebook groups set up for the purpose of the program (one per site to align with differing school term dates between sites). Project staff will post content to the Facebook group two times between each session. Each post will be related to the most recent conversation topics, and may include videos, links to articles and prompts to action. The aim is to provide participants with further information on the topic, prompt action in relation to the health behavior discussed at the previous session, encourage sharing of experiences, and increase social support. Facilitators will moderate posts (e.g., remove posts, pin, or unpin posts) and respond to comments posted by parents.

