### Statistical analysis

Statistical analyses will follow standard principles for RCTs using two group comparisons including all participants on an intention-to-treat basis. Between-group differences in the primary and secondary outcomes will be tested using a general linear mixed model, which accounts for the clustering of parent-child dyads within playgroups. Within each model, condition, time, the condition by time interaction will be included as fixed effects, with playgroup nested within condition, parent-child dyads nested within playgroup and condition, and the playgroup by time interaction nested within condition included as random effects.

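### Randomisation is stratified by site but the stated model has no site or site-by-time term, so tests are mildly conservative if sites differ in change over time

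*Protocol article*

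**What the plan says.** Study design describes a "multi-site cluster randomized controlled trial involving 60 community playgroups operating in three states across Australia", with 20 playgroups per state. Under Randomization, allocation, and blinding, "Group assignment for each site will be completed by an independent statistician using an allocation sequence generated by permuted block randomization", and "playgroups in each site will be randomized to the next condition (intervention or wait-list control) on the list". Site is therefore a stratification factor.

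Statistical analysis sets out the model. On the fixed side, "Within each model, condition, time, the condition by time interaction will be included as fixed effects". On the random side, "playgroup nested within condition, parent-child dyads nested within playgroup and condition, and the playgroup by time interaction nested within condition included as random effects". Neither list contains site.

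Sample size and power defines the target. For Aim 1, "the intervention effect is the net difference for change in the healthy lifestyle behaviors immediately post intervention and at 6-months follow-up". For Aim 2, "the intervention effect is the net difference for change in BMI z-score at 6-months follow-up". In the stated model both are condition-by-time contrasts.

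One other statement bears on the point. Signposting intervention explains that private Facebook groups are set up "one per site to align with differing school term dates between sites".

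**The concern.** Blocking within site balances the arms across states, so a difference between states cannot contribute to the true sampling variability of the treatment contrast. A model that ignores site still counts such a difference as playgroup variation when it estimates the standard error. Estimated standard errors are then larger than the true ones, confidence intervals are too wide, and tests reject too seldom under the null.

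For a difference in change, the component that matters is playgroup-by-time. It absorbs site differences in change, for instance if the programme and the later assessments fall at different calendar times in different states. At stake is precision that the stratified design has already secured and the stated analysis may not use.

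**Working it through.** **Inputs from Sample size and power and Table 2:** k = 30 playgroups per arm; m = 6 dyads per playgroup; two-sided alpha 0.05; ICC 0.10 (behaviours) and 0.02 (BMI z-score). Effect and SD: vegetables 38 and 58 g/d; discretionary foods 1.5 and 2 serves/d; physical activity (PA) 2 and 5 percentage points; screen time 30 and 75 min/d; sleep 40 and 96 min/d; BMI z-score 0.30 and 0.90.

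**Step 1: reproduce Table 2.** SE = SD × √(2[1 + (m − 1)ICC]/(km)). The design effect is 1.5 for behaviours and 1.1 for BMI z-score. Minimal detectable difference = (1.960 + 0.842) × SE. For screen time, SE = 75 × √(3/180) = 9.68 and the difference is 27.1 min. All six outcomes give 20.98 g, 0.72 serves, 1.81%, 27.1 min, 34.7 min and 0.279, against the printed 21, 0.7, 1.8, 27, 35 and 0.28. Power at the hypothesised effects (normal approximation) is about 87% for PA and screen time, 90% for sleep, 85% for BMI z-score and above 99.8% for the two dietary outcomes. The calculation takes no credit for stratification.

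**Step 2: does a site main effect help?** Three-visit data were simulated for 60 playgroups of 6 dyads, with the stated random effects and allocation balanced within site. Models were fitted by REML with and without a site main effect. In three data sets the SE of the condition-by-time contrast was 0.1145, 0.1233 and 0.1264 both ways. These values did not move when large stable site differences were added. Only the SE of the baseline condition effect shrank (0.217 to 0.118 in the first data set), and that is not the target.

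**Step 3: what if sites differ in change?** Let f be the share of the cluster (ICC) variance of the change that lies between sites. The documents do not give f; 0 to 0.5 is an assumption. The table's ICC is taken to apply to the change. In units of the SD squared, the variance of a playgroup mean is ICC + (1 − ICC)/6. This is 0.10 + 0.15 = 0.25 for behaviours and 0.02 + 0.1633 = 0.1833 for BMI z-score. The ratio of true variance to the variance the model estimates is

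r = [ICC(1 − f) + (1 − ICC)/6] / [ICC + (1 − ICC)/6].

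The SE without site-by-time is too large by 1/√r − 1. Its true type I error is 2[1 − Φ(1.96/√r)].

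| f | r, behaviours | SE excess | Type I | r, BMI z | SE excess | Type I |
|---|---|---|---|---|---|---|
| 0 | 1.00 | 0% | 5.0% | 1.000 | 0% | 5.0% |
| 0.10 | 0.96 | 2.1% | 4.55% | 0.989 | 0.6% | 4.9% |
| 0.25 | 0.90 | 5.4% | 3.9% | 0.973 | 1.4% | 4.7% |
| 0.50 | 0.80 | 11.8% | 2.8% | 0.945 | 2.8% | 4.4% |

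**Step 4: power at the hypothesised effects (d).** Without the term: Φ[(d/SE − t₅₈)/√r], with t₅₈ = 2.002. With it: noncentral t on 56 df, noncentrality d/(SE√r).

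| f | Screen time, PA: without → with | Sleep | BMI z |
|---|---|---|---|
| 0.10 | 86.8 → 87.4% | 89.5 → 89.9% | 84.6 → 84.6% |
| 0.25 | 87.6 → 89.4% | 90.2 → 91.7% | 84.8 → 85.2% |
| 0.50 | 89.0 → 92.6% | 91.5 → 94.4% | 85.1 → 86.2% |

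The largest gains are about 3.6, 2.9 and 1 point. Vegetables and discretionary foods stay above 99.8% either way. At f = 0, noncentral t for both analyses gives 86.1% for screen time and PA with 58 or 56 df. The lost degrees of freedom therefore cost about 0.1 point at most.

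**The case against.** The strongest reply is that nothing the article claims is harmed. The target is a difference in change, so stable state differences cancel. Table 2 assumes no gain from stratification, and any error is in the conservative direction. All of that stands.

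A reader might infer from the omission that power is lost outright, or that the inference is invalid. The documents support neither. Loss occurs only if sites differ in change, and at a zero share there is none. False positives are not inflated, and every power figure above stays over 80% without the term.

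Textual support for site differences in change is also thin. The remark about term dates explains how the Facebook groups are organised and says nothing about outcomes. It makes such differences plausible and gives no size.

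Finally, this is a condensed article, and an unseen analysis plan may name site as a covariate. That carries less weight here. The Statistical analysis section is not silent: it lists the terms down to the nested random interaction. The point concerns a stated model that omits the factor on which randomisation is stratified.

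**Conclusion.** The point holds as a minor mismatch between design and analysis. If sites differ in change, the stated model gives somewhat large standard errors and mildly conservative tests. Over the assumed 0% to 50% share the effect is modest for the behaviours, small for BMI z-score, and of no consequence for power on vegetables and discretionary foods.

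These figures rest on three assumptions: the assumed share, the stated ICCs applying to the change, and complete data with arms balanced within site. With attrition of up to 25%, incomplete data bring in some between-playgroup information, so a site main effect could then matter slightly. That was not quantified.

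**What to change.** Add site (three levels) and site-by-time as fixed effects to the model under Statistical analysis, for the primary and secondary outcomes, and fix this before outcome data are seen by arm. Site-by-time is the term that does the work for a difference in change; site alone is not enough.

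The cost is one sentence. Each change contrast gives up 2 of about 58 between-playgroup degrees of freedom. The three-visit model gains 6 fixed-effect parameters (2 for site, 2 × 2 = 4 for site-by-time). If the terms are left out on purpose, the plan should say why.
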